### Study Design

#### Overview

The study was approved by the local research ethics authority. This is a cluster randomized feasibility trial assessing 4 rural regions (2 per study arm) comparing usual rural community-based dementia care to Telegerontology plus usual rural community-based dementia care. Using the opaque envelope method, the rural regions will be randomized to control or intervention after baseline assessment. The intervention will last 6 months with the measurement of outcomes taking place at baseline, after 6 months (post), with follow-up occurring 6 months (6-month follow-up) and 12 months (12-month follow-up) after cessation of the intervention.

The study population will include 22 “dementia triads” that consist of a community-dwelling older Canadian with moderate to late dementia, their family caregivers, and their PCP. The study will be carried out in communities located in rural areas of Newfoundland and Labrador, Canada but will be monitored remotely from the metropolitan city of St John’s, Newfoundland and Labrador. We define *rural* in this study to mean a community with less than 10,000 residents and a location that is greater than two hours’ drive from the metropolitan city, where specialist health services are located. Before randomization, recruitment will begin by enrolling PCPs from rural communities who will make initial contact with potential participants. Written informed consent will be obtained for every individual agreeing to participate in the study except in the case for an individual with advanced dementia who lacks capacity, in which case consent will be obtained from the substitute decision maker. Consent will be reviewed without the presence of the PCP in order to limit undue influence for participation in the study.

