#### Primary Outcomes

Primary outcomes will be reported by caregivers and confirmed through medical records and chart reviews (schedule of assessment described in Table 1). Based on Canadian incidence rates, we anticipate these outcomes will be detectable during the 18-month study period [33-35]. The primary outcomes will be as follows:

Admission to long-term care (LTC): Date that participant is admitted to LTC.Emergency room (ER) visits: Total number of ER visits over 6 months.Falls: Total number of falls over 6 months.Hospital stays: Total number of hospital stays over 6 months.Caregiving Hassles Scale: This 42-item scale assesses the daily burden of caring for a family member with dementia. Caregivers are asked to rate patient requirements and behaviors on a 5-point scale of frequency, ranging from “Did not occur” to “A lot.” High scores indicate higher level of caregiver burden. Assessment takes 20 minutes to complete [28]. Administered by iPad, at pre, post, 6- and 12-month measures, in addition to an outcome measure, this scale will be used as a monitoring tool during the intervention at the discretion of the Telegeronology physician.

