### Clinical Assessment Tools

These tools will be used to help characterize the progression of dementia throughout the study and to inform clinical decision making (schedule of assessment described in Table 1). These assessments will also be used to address feasibility issues and to inform remote monitoring practices. All assessments will be administered by the physician or physiotherapist.

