### Sample Size Calculation

Sample size was calculated based on regional population statistics rather than for statistical power, targeting 2.5% of the population of community-dwelling dementia patients in the target region. Based on prevalence estimates, 98.5/1000 Canadians over 40 years of age have dementia with 34% living at home. The total population for the entire recruitment region of the present study is approximately 38,490 suggesting that the total population of community-dwelling dementia patents is approximately 1,289. Therefore, we aim to recruit 42 participants for inclusion in this study accounting for a 30% dropout rate.

**Table 2 table2:** Occupational Therapy Home Safety Video checklist.

Video	Description
1	A short video walking from the driveway outside, going into the house through the usual entry door, straight through the kitchen/living area into the person's bedroom and then into the bathroom.
2	Kitchen (short video)
3	Bedroom (short video)
4	Bathroom (short video)
5	Living room (short video)
6	Stairs (short video)
7	Laundry (short video)

Qualitative interview questions.PCP Interview QuestionsDescribe the care required to manage people with dementia in their homes.From your point of view, how well are your patients being managed at home?How would you envision an ideal circle of care to maintain people with dementia in their homes?Caregivers Interview QuestionsFrom your point of view, how well are you managing the health of your loved one at home?In an ideal world, how could things be improved? What are the main challenges you experience? Have you had successes caring for your loved one?

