### Statistical Analysis

Data entry, consistency check, and cleaning will be performed prior to analysis. Mean and standard deviation will be used for continuous variables, while frequency and percentages will be used to describe categorical variables. We do not anticipate this study will detect statistically significant findings however, as part of a secondary analysis, unpaired *t* tests will be used. Differences between intervention and control groups with respect to outcomes will be compared using repeated measures ANOVA or independent *t* test split by group. Data analysis will be conducted using SPSS statistical software. A *P*<0.05 will be used to determine potential significance. The 95% CI for differences will also be calculated. With respect to dropout, every person who is randomized regardless or subsequent fall, death, or admission to LTC will be included in the final analysis. If participants drop out before the intervention or voluntarily withdraw they will not be included in the final analysis. For analysis of the clinical assessments tracked over the course of the study (schedule of assessment described in Table 1), intention-to-treat analysis will be used by carrying the last observation forward.

Qualitative analysis will follow the Framework Method [47]. This method helps build rigor and trustworthiness in qualitative analysis by providing a clear audit trail from the original data to the final themes including illustrative quotations.

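### Last observation carried forward, labelled intention-to-treat, understates decline in the tracked dementia scores and can create a false arm difference in either direction

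*Protocol article*

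**What the plan says.** The Statistical Analysis section sets the rule for the repeated clinical assessments: "intention-to-treat analysis will be used by carrying the last observation forward". It names no other method or sensitivity analysis for these scores.

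Table 1 shows which tools are repeated at baseline, post, 6-month and 12-month follow-up: the Global Deterioration Scale, MMSE, MoCA, Cohen Mansfield Agitation Inventory and Cornell Scale. The intervention lasts 6 months, "with follow-up occurring 6 months (6-month follow-up) and 12 months (12-month follow-up) after cessation of the intervention", so the planned visits fall at months 0, 6, 12 and 18.

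The Clinical Assessment Tools section gives the purpose: "These tools will be used to help characterize the progression of dementia throughout the study". Footnote e of Table 1 ties the same tools to the remote-monitoring objective, which is to feed into the design of the full-scale trial.

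Three further statements bear on who has values carried forward:
- The Dropout section counts as dropout a voluntary withdrawal, or a failure to make contact within a month of a scheduled follow-up. It does not name death.
- The Statistical Analysis section keeps randomised people who fall, die or enter long-term care, but removes those who withdraw voluntarily or drop out before the intervention.
- The Sample Size Calculation section says "we aim to recruit 42 participants for inclusion in this study accounting for a 30% dropout rate", with no split by arm or reason.

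**The concern.** Carrying the last value forward assumes that nothing changes after the last visit. The study population is people with moderate to late dementia, and the stated purpose of these tools is to follow their progression. For the staging and cognitive scores the assumption therefore contradicts the reason for measuring them.

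The people most affected are those who cannot be reached, and those who die or enter long-term care and are no longer assessed. Because people who die stay in the analysis, the rule read literally gives them scores at visits after death. Filled-in values are also treated as if observed, which overstates how much is known.

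The main stake is the trajectories passed to the full-scale trial, which would look flatter than they are. A second stake arises if the arms are compared on these scores: unequal loss can then appear as an effect of the intervention. Unequal loss is plausible, since only the intervention arm has weekly calls and failed contact counts as dropout.

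**Working it through.** **1. The plan's own figure.** The recruitment target is the only derived figure that uses the dropout rate. 38,490 × 0.0985 × 0.34 = 1,289.0; × 0.025 = 32.2; × 1.30 = 41.9, which rounds to the stated 42. So 30% is an overall recruitment allowance. It is not an estimate of the share of scores carried forward.

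**2. Whose values are carried forward.** Dropout under the Dropout section is withdrawals plus people not contacted. The Statistical Analysis section takes withdrawals out and keeps deaths and long-term care admissions in. The carried-forward group is therefore the people not reached, plus the dead, plus admissions no longer assessed. Compared with the 30%, removing withdrawals lowers the share and adding deaths raises it. The share cannot be derived from the document.

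**3. Error per person (illustration).** Assumptions not in the document: linear MMSE decline of 2-4 points per year and no true arm difference. Error at month 18 = yearly rate × (18 − month last seen)/12.

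| Last seen | Years frozen | Error at 2 per year | Error at 4 per year |
|---|---|---|---|
| Baseline | 1.5 | 3 | 6 |
| Month 6 | 1.0 | 2 | 4 |
| Month 12 | 0.5 | 1 | 2 |

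**4. False arm difference, similar timing in both arms.** Multiply by an assumed 20-point difference in loss:
- last seen at baseline: 0.20 × 3 to 6 = 0.6 to 1.2 points
- last seen at month 6: 0.20 × 2 to 4 = 0.4 to 0.8 points
- last seen at month 12: 0.20 × 1 to 2 = 0.2 to 0.4 points

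The overall range is 0.2 to 1.2 points. With 22 triads split evenly (assumed), 20 points is 0.20 × 11 = 2.2, or about two people.

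**5. Understated decline.** Suppose 30% of month-18 values were carried forward, with last visits spread evenly over months 0, 6 and 12. The mean frozen time is (1.5 + 1.0 + 0.5)/3 = 1.0 year, so the mean error per person is 2 to 4 points and the understatement is 0.30 × 2 to 4 = 0.6 to 1.2 points. As a proportion, the decline shown is 0.70 + 0.30 × (0 + 6 + 12)/(3 × 18) = 0.80 of the true decline. With equal loss in both arms there is no false difference, but a true one shrinks by 20%.

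**6. Does the direction always favour the arm losing more?** Fraction of decline shown = (1 − loss) + loss × (month last seen/18).
- 20% against 40% loss, last visits spread evenly in both: 0.867 against 0.733. The arm losing more looks more stable, by 0.133 of the decline.
- 40% lost after month 12 against 20% lost after baseline: 0.60 + 0.40 × 12/18 = 0.867, against 0.80. The arm losing fewer now looks more stable.

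So the direction depends on timing as well as on amount.

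**The case against.** The strongest reply is that little rides on these scores. They are not primary or secondary outcomes, and Table 1 maps them to the remote-monitoring objective rather than to the test of Telegerontology. The planned group comparison refers to outcomes, so an arm contrast on MMSE or MoCA is not clearly planned. The trial is a feasibility study, not sized for power, and it expects no significant findings. All of this stands. It limits the consequence to descriptive trajectories, to any arm comparison made from them, and to what the next trial inherits. It does not make the rule suitable for describing progression.

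Three stronger readings are tempting, and the document does not support them:
- *The arm losing more people will look more stable.* This holds only when loss is similarly timed in the two arms (step 6).
- *The bias is known in direction for every tracked scale.* Agitation and depression scores need not worsen steadily, so no direction can be given for them.
- *About 30% of the 18-month values will be carried forward.* Withdrawals are excluded and deaths are not named in the dropout definition (step 2).

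A fair objection also applies to the remedy. A mixed model assumes data missing at random and does not by itself settle how deaths are handled.

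**Conclusion.** The point holds for the tracked clinical assessments. For the Global Deterioration Scale, MMSE and MoCA, the fixed rule understates decline, extends scores past death and treats filled-in values as data. Unequal loss can add a false arm difference in either direction.

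The sizes in steps 4 and 5 (0.2 to 1.2 points of false difference, 0.6 to 1.2 points of understated decline) are illustrations. They rest on an assumed linear decline of 2-4 MMSE points per year, an assumed 20-point gap in loss at similar timing, and an assumed 30% carried forward. None of these is in the document. The effect on standard errors was not quantified.

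The label is wrong as well. An analysis that removes voluntary withdrawals is not intention-to-treat, whatever is done with the remaining missing values.

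A reader might infer that the primary or secondary results are compromised. The rule is not stated for those outcomes. The Caregiving Hassles Scale is listed as an outcome measure and is not clearly covered by it. The change is worth making, mainly to protect what the full-scale trial will take from this one.

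**What to change.** In Statistical Analysis, replace last observation carried forward for these scores with a likelihood-based mixed model on all observed values, which the named software fits through SPSS MIXED:

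- Terms: baseline score, time, arm and arm-by-time. Enter region as a random effect, or show results by region. With two regions per arm, region is nested in arm and cannot be a fixed effect beside it.
- Include the observed scores of people who withdrew after randomisation. A person seen only at baseline adds nothing to a model that uses baseline as a covariate, so such people must appear in the missing-data table.
- Carry nothing past death, and state that scores are interpreted as while alive.
- Tabulate deaths and missing scores by arm, visit and reason.
- Keep the carried-forward analysis at most as a sensitivity display, and drop the intention-to-treat label from it.

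The cost is revised wording and a different procedure in the same software, with no new data. The downside is reliance on missing at random, which loss through decline or failed contact may violate. The model must also stay simple: with four regions the between-region variance will be poorly estimated, so results by region should be readable on their own.

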## Results

Recruitment began in January of 2014. Data collection was completed in April 2017. Results will be available in March of 2018.

## Discussion

### Significance of Study

The proposed study is the first study, to our knowledge, to use Telegerontology together with Skype and specialized remote monitoring apps for the iPad to optimize health and safety among rural community-dwelling Canadians with dementia. The results could have particular importance given the international increase in prevalence of dementia [48], and the shift away from institutional-based models of care in Canada and other countries [49].

### Study Strengths and Limitations

The proposed study has several notable methodological strengths. The initial home visit is designed to help build rapport between the Telegerontology physician and participants. This method is also in keeping with previous research, which suggests that telehealth has effectively supported assessment and follow-up when used in combination with an in-person interdisciplinary memory clinic assessment [12].

Next, the Telegerontology measurement framework, based on the ICF and Wilson-Cleary models provides in-depth, multi-factor profiles of participants contributing to a methodology that acknowledges the broad range of factors that can impact health planning and management of community dwelling people with dementia. Likewise, the inclusion of caregivers and PCPs as participants adds further depth to both characterizing and assessing participants with dementia by acknowledging and building on the role of the caregiver and PCP in the health care triad. The development of remote monitoring apps from existing validated scales to assess dementia and caregiver burden is also a methodological strength of this study.

There are also several limitations in the protocol. The relatively small sample size can be seen as a drawback, however, based on regional prevalence estimates, the sample size is realistic for the target population. There may also be considerable variability between participants within a group, further complicating statistical analysis. Next, the Telegerontology physician serves as both an interventionist and assessor. This has the potential to create bias, however the primary outcome measures were selected partially to address this issue since they are based on participant self-report/chart review rather than clinical assessment.

### Conclusion

This proposed study will provide an evaluation of Telegerontology together with Skype and specialized remote monitoring apps for the iPad to optimize health and safety among rural community-dwelling Canadians with dementia. Results from this study will demonstrate a novel approach to dementia care that has the potential to impact both rural PCPs, family caregivers, and people with dementia, as well as provide evidence for the utility of Telegerontology in a full scale RCT.
